## Abstract

Introduction: Responsive caregiving is one of the most fundamental pillars of early childhood development. In the newborn stage, the parents are undergoing transitions and require support to understand the nuances of interacting with the young baby. The role of healthcare facilities in this becomes vital as a hub for conducting parenting education sessions that may yield thriving outcomes for young children and their future development. This study aims to explore the impact of the early childhood newborn parenting program on parental confidence and newborn responsive interaction and to explore the perceptions of healthcare providers regarding the intervention implemented in healthcare settings.

Methods: An implementation research design will be used in this study. A total of 500 participants will be included in the study, 400 from Pakistan and 100 from Afghanistan. There are two sites: each site will be randomly assigned as a control or an intervention. The rationale was to ensure that both sites are in different geographical locations. Participants from each side will be chosen using a convenience sampling technique. Cohort 1 (control group) will only be provided with a self-study, one consolidated handout on responsive caregiving, and one-time bed teaching, and will be requested to visit the center after six months (child age) for an endline. While cohort 2 (intervention group) will be provided a six-module intervention consisting of one session at birth with a self-study handout on responsive caregiving, and five monthly sessions (once a month till the infant turns six months) will be conducted. Outcomes measured at the baseline and endline (at six months) include differences in responsive interactions and parenting confidence scores between the control and intervention groups using tools such as Karitine parenting confidence, responsive interaction scale, Caregiver Reported Early Development Instruments (CREDI), WHO QoL, and Patient Health Questionnaire (PHQ).

Results: This is an ongoing study protocol, and the analysis of the results is expected in December 2025.

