**Figure 1 FIG1:**
[figure not shown]
Flow chart of the study procedure

Study setting

Participants will be recruited from the six basic health centers (BHCs) of not-for-profit private healthcare systems in Pakistan and Afghanistan. These BHCs will be chosen as primary healthcare facilities to pilot the intervention, as shown in Tables 1-2. The BHCs provide maternal, newborn, and child health services (MNCHS), including antenatal care, delivery, and postnatal care (ANC-PNC), family planning, immunization, adult health screening, and regular growth monitoring of <3 years old. Through lady health visitors (LHVs), responsive parenting education will be integrated into their maternal and newborn care model.

**Table 1 TAB1:** Field sites (Pakistan) F4HE: Foundations for Health and Empowerment

S/n	Site Selection	Location of Health Facility	Type of Health Facility	Level of Services	Average Deliveries Per Month	Covering Under F4HE Geographical Areas
1	Pakistan Intervention Group Site 1 (PIGS 1)	District Upper Chitral	Basic Health Center	Primary	10	Yes
							Pakistan Intervention Group Site 2 (PIGS 2)	District Lower Chitral	Basic Health Center	Primary	4	Yes
	2	Pakistan Control Group Site 1 (PCGS 1)	District Upper Chitral	Basic Health Center	Primary	10							Yes
							Pakistan Control Group Site 2 (PCGS 2)	District Lower Chitral	Basic Health Center	Primary	4	Yes	

**Table 2 TAB2:** Field sites (Afghanistan) F4HE: Foundations for Health and Empowerment

S/n	Site Selection	Location of Health Facility	Type of Health Facility	Level of Services	Average Deliveries per Month	Covering Under F4HE Geographical Areas
							1	Afghanistan Intervention Group Site 1 (AIGS 1)	Baharak District	District Hospital (DH)	Primary and Secondary	265	Yes
							2	Afghanistan Control Group Site 1 (ACGS 1)	Jurm District	Comprehensive Health Center (CHC)	Primary	77	No

Eligibility criteria

Inclusion criteria for the study enrolment are (i) the newborn’s mother following a normal delivery; (ii) the newborn does not exhibit any underlying morbidities; (iii) the family is not living in ultra-poverty with less than 15,000/- total household income; and (iv) the family can understand Urdu. The exclusion criteria for the study include (i) newborns with underlying conditions or morbidities, (ii) the family living on a 15,000 household income per month, and (iii) mothers with postpartum depression.

Study intervention

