A total of 500 participants will be chosen, 100 from four primary healthcare facilities in the regions of Chitral, Pakistan, and 100 from two primary healthcare facilities in Afghanistan. A total of 200 before-intervention participants as a control group and 200 intervention participants in Pakistan will be recruited. Similarly, for Afghanistan, 50 pre-intervention (control) participants and 50 intervention participants will be recruited as a control group. The sample size is chosen based on convenience sampling, and the facilities are selected considering the number of deliveries and outreach feasibility. It is anticipated that 40% of the total annual deliveries may consent to participate, and based on calculations, this will help us achieve our N for each of the cohorts. Additionally, there might be variations in the actual data collection.

Data collection plan

We will have two cohorts: a cohort before the intervention and an after-cohort with the intervention. Each cohort will last for six months.

Cohort 1 (control group): Baseline data will be collected, and they will be provided with a self-study pictorial module. They will be tracked and requested to visit the center at six months (child age) post-delivery. At six months, their endline data on responsive interactions, parenting confidence, and patient experience will be collected.

Cohort 2 (intervention group): Baseline data will be collected, and they will be provided a six-month intervention consisting of one session at birth with a self-study manual, and five monthly sessions (once a month till the infant turns six months). At six months, they will also be assessed on the measures mentioned above, and endline will be collected.

Data analysis

Both qualitative and quantitative data analysis strategies will be used to conduct data analysis.

Quantitative analysis will be performed using the statistical package for the social sciences (SPSS Inc., Chicago, IL). Descriptive statistics, such as frequencies, percentages, means, and SD, will be computed for demographic characteristics, QoL, and parental outcomes (confidence, feeding, and teaching assessment using KPSC, NBRI score). Independent sample t-test, paired test, and repeated measure ANOVA will be used to compare within and between-subject effects. Multilevel logistic regression will also be performed for categorical outcomes to observe the effectiveness after controlling for the confounding factors. P≤0.05 will be considered significant.

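### The Pakistani arms are balanced by district, but the tests named for the continuous outcomes pool the districts; stratifying by Upper and Lower Chitral would remove any district-mix bias at almost no cost

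*Protocol article*

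**What the plan says.** - **Sites.** Table 1 (Field sites, Pakistan) lists four basic health centers at primary level. Each arm has one in Upper Chitral with 10 deliveries a month and one in Lower Chitral with 4 a month.
- **Targets.** The section on sample size, recruitment and enrolment sets the Pakistani numbers by arm: "A total of 200 before-intervention participants as a control group and 200 intervention participants in Pakistan will be recruited". Sampling is by convenience, and one anticipated consent figure, 40% of annual deliveries, is given for all facilities.
- **An unclear facility count.** The same section opens with "A total of 500 participants will be chosen, 100 from four primary healthcare facilities in the regions of Chitral, Pakistan", whereas the Abstract says "A total of 500 participants will be included in the study, 400 from Pakistan and 100 from Afghanistan".
- **Tests.** The Data analysis section says: "Independent sample t-test, paired test, and repeated measure ANOVA will be used to compare within and between-subject effects". No district or facility term is named. The next sentence adds a multilevel logistic regression that controls for confounders, for categorical outcomes only. The main outcomes in the Abstract, parenting confidence and responsive interaction, are scores.
- **Timing and follow-up.** The Data collection plan describes a cohort before the intervention and a later one with it. Controls are asked to return at six months; intervention mothers have monthly sessions.

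**The concern.** The sites are not securely randomised: the Abstract says random assignment, while the Study design section says the sites are divided by convenience. Having both Chitral districts in both arms is therefore a useful source of comparability for the 400 Pakistani mothers out of 500, and the named analysis of the scores does not use it.

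A pooled comparison of arm means is free of district effects only when the share of Upper Chitral mothers among those analysed is the same in both arms. If the shares differ, part of any outcome difference between the districts appears as an intervention effect. If the shares are equal, pooling leaves district variation in the error term and costs a little precision.

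**Working it through.** **1. The plan's own accrual figure.** Deliveries per Pakistani arm: (10 + 4) × 12 = 168 a year. At 40%: 168 × 0.40 = 67, against a target of 200. Reaching 200 at that rate takes 200 / (14 × 0.40) = 36 months. The statement that 40% of annual deliveries achieves the cohort size is thus not reproduced for Pakistan within a year. That is a separate problem. It matters here because recruitment will have to depart from the stated assumption (higher uptake, longer accrual or a shortfall), so equal mix cannot be taken for granted.

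**2. District mix on the stated inputs.** With uniform consent, the Upper Chitral share is 10/14 = 71.4% in each arm, about 143 and 57 of 200. The share gap is 0, the expected bias is 0 and the type I error is 5%.

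**3. Mix if 100 is a facility quota.** 4 × 100 + 100 = 500 agrees with the Abstract; 100 + 100 = 200 does not. Under the quota reading each arm is 50:50 and the expected bias is again 0. At 4 deliveries a month and 40% consent, however, a Lower Chitral center needs 100 / 1.6 = 62.5 months to reach 100, or 25 months with everyone consenting. The quota reading cannot be relied on to fix the mix.

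**4. Bias if the mix differs.** Bias = (Upper Chitral share in the intervention arm − share in the control arm) × district mean difference. The documents give neither differential consent nor a district effect, so both are assumptions. The share is 10a / (10a + 4b), with consent a in Upper and b in Lower Chitral.

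| Assumed consent, Upper/Lower: intervention vs control | Shares | Gap | Bias at 0.2 SD | Bias at 0.5 SD |
|---|---|---|---|---|
| 45/35% vs 35/45% | 0.763, 0.660 | 0.102 | 0.02 SD | 0.05 SD |
| 50/30% vs 30/50% | 0.806, 0.600 | 0.206 | 0.04 SD | 0.10 SD |

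**5. Type I error of an unadjusted endline comparison.** Normal approximation, two-sided 0.05 (sidedness is not stated), within-district SD 1, n = 200 per arm. The variance in an arm is 1 + s(1 − s)d², where s is its Upper share and d the district difference; SE = √((v₁ + v₂)/200), about 0.10 SD.

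- Gap 0.102: 5.5% at d = 0.2 and 7.9% at d = 0.5.
- Gap 0.206: 7.0% at d = 0.2 and 17.2% at d = 0.5. The last case has bias 0.103, SE 0.102 and ratio 1.01.
- If only 67 per arm are reached, the SE is about √(2/67) = 0.17 SD and the same four cases give 5.2% to 9.0%.

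**6. Precision cost with equal mix.** SE ratio, pooled to stratified = √(1 + (10/14)(4/14)d²): 1.004 at d = 0.2 and 1.025 at d = 0.5.

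**The case against.** The strongest reply is that the document's own inputs give no bias at all: equal volumes and one consent rate in both arms, or a quota of 100 per facility. This stands as a statement about expectation. It does not stand as a guarantee, because the consent rate cannot deliver the target within a year, the quota reading is implausible at the listed volumes, and the mix that counts is that of the mothers who return at six months.

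Second, a stable difference in level between districts cancels in the group-by-time term of a repeated-measures ANOVA. This is correct, so the figures above apply mainly to endline t-tests. In the group-by-time term, bias arises only if the districts change differently.

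Third, covariates may be specified in a full protocol or SAP that is not shown. That is fair for the list of confounders. But the article itself restricts confounder control to categorical outcomes and names unadjusted tests for the rest, which is a stated choice.

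Three stronger readings are tempting and not supported:

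- A reader might infer that a matched design has been discarded. The article never declares matching or pairing; it shows only a symmetric layout.
- A reader might infer that every between-arm analysis ignores district. The multilevel logistic model may include it; its levels and covariates are not listed.
- A reader might infer very large error inflation. A 0.5 SD district difference with a 30-point gap would give a bias of 0.15 SD and a type I error of 32%, but that needs two large assumed inputs together, and nothing in the document makes either likely.

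**Conclusion.** The point holds as a cheap improvement, not as a demonstrated bias. The Pakistani layout allows a within-district comparison, and the analysis named for the scores does not make it. Under the assumptions in the table, the bias is about 0.02 to 0.10 SD and the type I error about 5.5% to 17% at 200 per arm, less if fewer are recruited. With equal mix the loss is only 0.4% to 2.5% in the SE.

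The point is confined to Pakistan. In Afghanistan (Table 2) the intervention facility is in Baharak and the control facility in Jurm, so district and arm coincide and stratification cannot separate them. Within each Chitral district there is one facility per arm, so differences between facilities remain confounded with the intervention whatever is done about district.

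**What to change.** 1. In every between-arm model for Pakistan, continuous and categorical, include district (Upper or Lower Chitral) as a fixed stratum. In the repeated-measures model this means district and its interaction with time, because a main effect alone does not protect the group-by-time term.
2. Report the intervention-minus-control difference within each district beside the combined estimate.
3. Reconcile the count of 100 given for the four Chitral facilities with the Pakistani total of 400.
4. Set the same recruitment target for the two facilities of a district, whatever split between districts is chosen.

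Items 1 and 2 set the expected district-mix bias to zero under any pattern of consent between districts, and also cover district mix that shifts through unequal return at six months, which recruitment targets cannot. The cost is one sentence on targets, one stratum in the models and two extra reported differences. The downside is that the faster facility of a district must stop at the common target. The write-up should say that facility-level confounding remains and that the remedy does not extend to Afghanistan.

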## Materials and methods

Study design

This before-and-after implementation feasibility study will examine the feasibility, fidelity, and adaptation of this intervention in the primary healthcare settings of remote Pakistan and Afghanistan. Implementation research is a relatively new approach in the medical sciences, but it has been widely used in various global, public health, and social sciences research. It also has great potential to allow flexibility for the researchers to be engaged and involved in the process of research. The field sites will be conveniently divided into two groups. The intervention and the control. The intervention group will undergo a structured responsive parenting education program, i.e., six sessions in the first five months of life on a structured curriculum under the supervision of trained lady healthcare workers, while the control group will undergo limited intervention, i.e., a compiled handout at birth for self-study (outlined in Figure 1). 

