There will be a structured training whereby internationally trained master trainers in ECD and Keys to Infant Caregiving from Parent-Child Relationship Programs, at Barnard Center, University of Washington and internally certified on ECD PREP ObGyn Aga Khan University curriculum, will provide training to the field site investigators and coordinators, who will then cascade the training to the lady healthcare workers at each study setting. After receiving training, the trained healthcare providers will deliver the content in group-based teaching sessions. Each lady healthcare worker will be selected based on their prior experience in patient and family education by the healthcare facility lead and will undergo a four-day structured training program. Additionally, they will have monthly mentoring check-ins throughout the intervention and will be provided with constant support and random first-hand check-ins by the field coordinators, who will go and co-conduct and observe the session with them. The whole intervention will be closely supervised by the field co-investigators and the lead investigator. An assigned research specialist will conduct monthly meetings to provide the support needed at the field sites.

Ethical considerations

This proposal has received approval from the National Bioethics Commission (No.4-87/NBCR-986/23/323), Pakistan, the Aga Khan University ethical review committee (ERC # 2023-8343-24153), and the Institutional Review Board of Afghanistan (IRB Code No: A-8-24-445). Informed written consent will be sought from all the participants. They will be informed about all the modalities involved in the research project, their rights, and, in no form, will there be names or any identifiable information that will be sought or recorded. All forms will have a unique participant code. All the data will be kept confidential. The data collectors will collect the forms, seal the forms, and send them to the main institution. Additionally, the data will be kept in lock and key. Until the forms are sent here, all the data on the field sites will also remain in a locked drawer.

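### Consent follows allocation and asks far more of intervention mothers, so the arms may differ in who agrees, and no adjustment is stated for the continuous outcomes

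*Protocol article*

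**What the plan says.** **Allocation.** The Abstract says "each site will be randomly assigned as a control or an intervention". Study design says "The field sites will be conveniently divided into two groups". The Data collection plan speaks of a cohort before the intervention and one with it. These accounts conflict, but in all of them a mother's arm is settled before she is approached.

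**Commitment, control arm** (Data collection plan): "They will be tracked and requested to visit the center at six months (child age) post-delivery".

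**Commitment, intervention arm** (same section): a session at birth, then "five monthly sessions (once a month till the infant turns six months", then the endline. Delivery of the intervention adds that "the trained healthcare providers will deliver the content in group-based teaching sessions". No sentence gives the venue of the monthly sessions. The facility is the natural reading, since the Abstract presents healthcare facilities as the hub for such sessions.

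**Consent** (Ethical considerations): "They will be informed about all the modalities involved in the research project".

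**Uptake** (Sample size, recruitment, and enrolment): "It is anticipated that 40% of the total annual deliveries may consent to participate", and "this will help us achieve our N for each of the cohorts". No arm-specific figure is given.

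**Safeguards.** The eligibility criteria contain nothing on availability or access. The Data analysis section names t-tests, paired tests and repeated measures ANOVA. It mentions control of confounding only with multilevel logistic regression for categorical outcomes. The limitations section names low generalizability and underrepresentation, but not selection that differs between arms.

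**The concern.** When arm is known before consent and the arms ask for different things, the mothers who agree can differ by arm even if every eligible mother is approached in the same way. In remote districts, agreeing to come every month plausibly depends on distance, help at home and motivation. Those same traits plausibly relate to parenting confidence, interaction and quality of life.

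Objective 1 is a between-arm comparison of confidence and interaction. If consenters differ, part of any observed difference reflects who joined and not what the programme did. The planned analysis of these scores names no covariate that would address this.

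**Working it through.** **1. The plan's own uptake figure.** Expected yearly recruits = monthly deliveries (Tables 1 and 2) × 12 × 0.40.

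| Setting | Deliveries per year | 40% | Target |
|---|---|---|---|
| Pakistan, each arm | (10 + 4) × 12 = 168 | 67 | 200 |
| Afghanistan, intervention | 265 × 12 = 3180 | 1272 | 50 |
| Afghanistan, control | 77 × 12 = 924 | 370 | 50 |

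The 40% reproduces none of the targets. Afghanistan needs 50/3180 = 1.6% and 50/924 = 5.4% of a year's deliveries. Pakistan would need 200/168 = 119%. The shortfall in Pakistan is a separate matter. It matters here because it shows that 40% does not govern who enters at any site, so it cannot be read as the selection mechanism.

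**2. Commitment by arm.** Control: one return. Intervention: five monthly sessions plus the endline.

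**3. Illustrative size. All inputs are assumptions except the 250 per arm (200 + 50).** Suppose consent goes to the top fraction p of a standard normal trait. The mean trait among consenters is φ(z_p)/p:

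- p = 0.40: 0.966
- p = 0.50: 0.798
- p = 0.60: 0.644
- p = 0.70: 0.497

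With 40% uptake in the intervention arm, the trait gap is 0.168, 0.322 or 0.469 SD against control uptake of 50%, 60% or 70%. Bias in the score = r × gap, where r is the trait-outcome correlation. For r from 0.2 to 0.5 this spans 0.2 × 0.168 = 0.03 to 0.5 × 0.469 = 0.23 SD.

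For an unadjusted endline comparison, SE = √(2/250) = 0.089 SD, ignoring clustering. The false-positive rate is P(|Z + bias/SE| > 1.96), taking the test as two-sided:

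- 40% vs 60%, r = 0.3: bias 0.097 SD, rate 19%
- 40% vs 70%, r = 0.3: bias 0.141 SD, rate 35%
- 40% vs 40%: bias 0, rate 5%

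**4. Sensitivity.** Step 3 lets one trait determine consent completely. If the trait correlates only 0.5 with the propensity to consent, 0.097 becomes 0.5 × 0.097 = 0.048 SD and the rate falls to about 8%. If uptake is higher in the intervention arm, the sign reverses.

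**5. What the baseline does.** In a comparison of change (the group-by-time term), with scores in the same SD units, bias = (r_end − r_base) × gap. If the trait relates equally to both scores, this is zero. If it relates at 0.3 to the six-month score and not at all to the score at birth, the full 0.097 SD remains. Baseline measurement therefore removes a stable difference in level, but not a difference in how mothers change over six months.

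**The case against.** The strongest reply has five parts.

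- **Direction is not shown.** A reader might infer that consent selects more able and motivated mothers into the intervention arm and so favours the programme. The article gives no uptake or consenter characteristics by arm. The offer of six taught sessions could raise uptake, or attract less confident mothers. This stands: the direction is unknown.
- **The 40% causes nothing.** A reader might take the common rate as the fault. It is a feasibility guess, equal uptake gives zero bias in the model above, and separate guesses per arm would remove none. This stands.
- **Baseline scores are collected in both arms, and repeated measures ANOVA is planned.** This stands in part, as step 5 shows. It also defeats any claim that the difference could not be dealt with later. Education and socio-economic status are on the demographic form, and the form's published list is open-ended, so travel time cannot be said to be absent from the form itself.
- **The contrast may be overstated.** The venue is inferred. The centers also provide immunization and growth monitoring, so some visits may happen anyway. The consent sentence could mean the same full description for every mother. These points reduce the likely size. They do not remove the risk, because the mother still joins an arm already fixed at her site or in her cohort.
- **The limits are declared.** The article calls the design quasi-experimental and recommends a randomized trial in future. It does not mention selection that differs between arms.

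**Conclusion.** The concern holds in limited form. Consent follows allocation, the commitment is unequal, nothing in eligibility offsets it, and no confounder adjustment is stated for the continuous outcomes. Differential selection is therefore a real and unaddressed risk, of unknown direction and size.

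The 0.03 to 0.23 SD range and the 19% and 35% false-positive rates are illustrations only. They rest on assumed uptake gaps, a single trait that fully determines consent, no baseline adjustment, 250 per arm recruited, and independent mothers despite only six facilities. They should not be read as estimates for this study. The documents do not support saying that the arms will differ, that the difference favours the programme, or that the 40% sentence produces it. This is a modest point, worth acting on because the remedy is cheap.

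**What to change.** 1. Before the arm-specific part of consent, ask every approached mother in both arms one identically worded question: whether she is able and willing to come to the center monthly until six months. Record travel time to the center. Exclude nobody on the answer. Restricting enrolment to those who say yes would narrow a feasibility sample and cut recruitment in Pakistan, where delivery volumes already fall short.
2. Compare endline confidence and interaction scores between arms in a model adjusted for the baseline score, travel time, stated availability and the socio-economic items already collected.
3. Add a sensitivity analysis limited to mothers in both arms who answered yes.
4. Report eligible, approached and consented counts by facility and arm.
5. Add selection that differs between arms to the limitations.

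**Cost.** Two form items, a recruitment log and slightly more analysis. A control mother's hypothetical yes only approximates an intervention mother's real acceptance, so some difference may remain. The article says the study is in progress, so the availability question cannot be asked before consent for mothers already enrolled. For them, travel time could still be recorded at the endline visit.

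### For Pakistan, 40% of annual deliveries does not give 200 mothers per cohort: Table 1 supports about 67 per arm per year, or about 134 per cohort-year if all four sites feed each cohort in turn

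*Protocol article*

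**What the plan says.** The Abstract sets the total: "A total of 500 participants will be included in the study, 400 from Pakistan and 100 from Afghanistan". The section on sample size, recruitment and enrolment divides the Pakistan share by cohort: "A total of 200 before-intervention participants as a control group and 200 intervention participants in Pakistan will be recruited". Afghanistan is to supply 50 and 50. The same section justifies these numbers by expected consent: "40% of the total annual deliveries may consent to participate, and based on calculations, this will help us achieve our N" for each cohort. The calculation it refers to is not shown.

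The delivery volumes are in Tables 1 and 2, in the column headed "Average Deliveries Per Month":

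- Pakistan, intervention: 10 (Upper Chitral) and 4 (Lower Chitral).
- Pakistan, control: 10 (Upper Chitral) and 4 (Lower Chitral).
- Afghanistan: 265 (intervention) and 77 (control).

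The opening sentence of the sample-size section gives a different Pakistan figure: "100 from four primary healthcare facilities in the regions of Chitral, Pakistan, and 100 from two primary healthcare facilities in Afghanistan". The data collection plan describes a cohort before the intervention and a cohort after it, and adds: "Each cohort will last for six months". The Results section places dissemination between December 2025 and March 2026.

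**The concern.** The recruitment statement is a positive numerical claim, and its inputs are printed in the same article, so it can be checked directly. The Chitral facilities are very small. A target of 200 per cohort exceeds a whole year's deliveries at the two sites labelled for either Pakistan arm.

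Four-fifths of the planned sample (400 of 500) rests on this statement. If it is wrong, either Pakistan enrols far fewer mothers than stated in a one-year period, or enrolment runs much longer than the reporting dates suggest. In the first case the country mix also changes, from 400:100 to about 134:100. In a study meant to show feasibility in primary care, the recruitment yield is itself one of the quantities of interest.

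**Working it through.** **Inputs.** Monthly deliveries come from Tables 1 and 2. The 40% and the cohort targets come from the sample-size section. The base for the 40% is total annual deliveries, as the article states.

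**Formulas.** Annual yield = monthly deliveries × 12 × 0.40. Months to reach N = N / (monthly deliveries × 0.40).

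**1. Where the statement can be reproduced: Afghanistan.**
- Intervention: 265 × 12 × 0.40 = 1,272 against 50.
- Control: 77 × 12 × 0.40 = 369.6 against 50.

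The claim holds with a wide margin.

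**2. Pakistan, with sites assigned to arms as Table 1 labels them.**
- Deliveries per arm: (10 + 4) × 12 = 168 a year.
- At 40%: 168 × 0.40 = 67.2 against 200, or 34% of target.
- Consent needed to reach 200 in a year: 200 / 168 = 119%. Even full consent gives only 168.
- Time to 200 per arm at 40%: 200 / (14 × 0.40) = 35.7 months, with both arms enrolling in parallel.

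**3. Pakistan, with all four sites feeding each cohort in sequence** (the before-and-after description).
- Deliveries: 28 × 12 = 336 a year.
- At 40%: 336 × 0.40 = 134.4 per cohort-year against 200, or 67% of target.
- At full consent: 336 per cohort-year, which would exceed 200.
- Time per cohort at 40%: 200 / (28 × 0.40) = 17.9 months. For both cohorts: 400 / (28 × 0.40) = 35.7 months.

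**4. Pakistan total per calendar year.** The yield at 40% is 134.4 against 400 on either reading.

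**5. What the undisclosed calculation might have used.** Two variants satisfy the claim.
- A Pakistan total of 100: 134.4 is enough.
- Both countries pooled: (14 + 265) × 12 × 0.40 = 1,339.2 and (14 + 77) × 12 × 0.40 = 436.8, against 250 per arm.

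Neither fits the stated allocation. The first uses the figure that conflicts with 400. The second relies almost entirely on Afghan deliveries, while 400 of the 500 participants are to come from Pakistan.

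**6. Timeline.** Enrolment of 35.7 months plus six months to the last endline is about 42 months. The article gives no enrolment start date. Counting back 42 months from December 2025 gives June 2022, and from March 2026 gives September 2022. Enrolment would have to have begun by about then.

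**7. Illustrative precision.** The article states no effect size, power or precision, so this only gives scale. The detectable difference is 2.80 × √(2/n) in SD units (80% power, two-sided 5%, clustering ignored).
- Pakistan alone: n = 200 gives 0.28 and n = 67 gives 0.48.
- Countries pooled, with Afghanistan meeting 50 per arm: n = 250 gives 0.25 and n = 67 + 50 = 117 gives 0.37.

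**The case against.** The best defence is that the article fixes no enrolment window, calls itself a feasibility study with a convenience sample, and discloses recruitment risk: the sample-size section allows for variation in actual data collection, and the limitations section says the target may be missed. This mitigates only in part. The limitations section attributes the risk to regime change and climate events, not to delivery volume. The claim itself is framed in annual deliveries, and a shortfall built into the article's own table is not an unforeseen event.

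The defence does succeed against several stronger readings that a reader might infer:

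- *Even full consent always falls short in a year.* This is true for the arm-specific sites in Table 1 (168 against 200). It is not true if each cohort has its own full year at all four sites (336). The article describes both designs.
- *Only about 34 per arm can be enrolled (14 × 6 × 0.40), because a cohort lasts six months.* The six months fit follow-up from birth to endline at least as well as an enrolment period.
- *The study's precision claims are wrong.* There are none to be wrong, and the article does not say whether the countries will be analysed separately or pooled.
- *Eligibility exclusions cut the 67 further.* The 40% applies to all deliveries and may already be net of ineligible mothers.
- *The 500 total does not add up.* It agrees with 400 + 100 in the Abstract and with 200 + 200 + 50 + 50 in the sample-size section. Only the 100 for the four Chitral facilities is out of line. A dropped word meaning 100 from each facility would explain it (4 × 100 + 100 = 500).

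**Conclusion.** The statement that 40% of annual deliveries achieves the planned N for each cohort is false for Pakistan under either description of the design, and true for Afghanistan. One year at 40% gives about 67 per Pakistan arm with the sites as labelled in Table 1, or about 134 per cohort if all four sites serve each cohort in sequence, against 200. Enrolling all 400 takes about 36 months in either case.

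This rests only on Table 1's average deliveries, the article's own 40%, and recruitment from deliveries at the listed facilities. The limitations section supports the last of these by tying the sampling to facility delivery volume. The size of the shortfall, one third of target reached or two thirds, depends on which design is meant. The full-consent shortfall holds only for arm-specific sites, or for enrolling all 400 in a single year (336 against 400). The effect on detectable difference is illustrative and depends on the analysis chosen. The point should be corrected, because a stated justification for most of the sample is contradicted by the article's own table.

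**What to change.** 1. Replace the 40% sentence with a calculation by facility: monthly deliveries, the consent proportion and whether it is net of eligibility, the enrolment months, and the resulting N per cohort. Say whether Pakistan sites are arm-specific or serve both cohorts in turn.
2. Then either restate the Pakistan target as what Table 1 supports (about 134 in total per 12 months of enrolment at 40%), or keep 400, state the roughly 36-month enrolment window plus six months to the last endline, and align the reporting dates. If the authors prefer to add facilities or shift the allocation towards Afghanistan, the same calculation should be shown for that plan.
3. Correct the figure of 100 for the four Chitral facilities so that it agrees with 400 from Pakistan and 500 overall, or with the restated N. Carry any change into the Abstract.
4. If a precision statement is added, give it for the restated N and say whether it is by country or pooled.

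Restating the N costs only edits to the sample-size section and Abstract, with a less favourable number in print. Keeping 400 is not merely rewording: it commits the study to about three years of enrolment. Adding facilities would cost training and supervision at the new sites.
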